## Abstract

**Introduction::**

This study provides a comprehensive overview of the materials and methods used to evaluate the effectiveness of the use of biofeedback in the treatment of aggressive episodes in children and adolescents.

**Background::**

Aggressive episodes are common in various disorders and are associated with deficits in emotional processing and impulse control, primarily due to dysfunctions in the amygdala and prefrontal cortex (PFC). These brain regions also regulate physiological arousal, influencing heart rate and other autonomic functions even before aggression manifests. These early signals can be shown to the person (biofeedback) reinforcing therapeutic skills to enhance emotional regulation and reduce aggression.

**Methods::**

A total of 70 participants will be recruited for a randomized controlled trial (RCT). All participants will receive therapy, although only the intervention group will incorporate biofeedback. The experimental study will be split into three blocks: (1) *Home Monitoring*: Physiological signals will be recorded using a smartwatch, and aggressive episodes will be captured with a camera; (2) *Laboratory Assessment*: Participants will attend three sessions, where therapists will induce aggressive reactions, using the video clips recorded at home. Simultaneously, real-time physiological signals will be measured. These sessions will also include relaxation periods before and after the provoked outburst; (3) *Therapeutic Intervention:* Similar to the laboratory assessment block, therapists will induce aggressive responses in three sessions; however, in this block, participants will receive therapy. Additionally, participants who belong to the intervention group, will include biofeedack in the therapy. Biofeedback is focused on heart rate (HR), heart rate variability (HRV), and skin conductance level (SCL). The CACIA, the Stroop, and other pre- and post-experimental tests. will be used to assess the differences between the control and intervention groups.

**Discussion::**

Emotions play a fundamental role in decision-making, social interactions, and mental health. Emotional dysregulation often leads to aggression, irritability, and anxiety. Showing physiological responses to patients, such as heart rate variability and skin conductance, may improve emotional awareness and regulation. This study aims to verify the effectiveness of including biofeedback in such therapy.

## Introduction

Aggression is a common symptom that is frequently addressed by mental health professionals, yet it continues to be one of the most complex issues to treat. From a psychiatric-diagnostic perspective, aggressive behavior has been subsumed under specific diagnoses of conduct disorder (CD) and oppositional defiant disorder (ODD), although many other disorders can also affect behavior, e.g., autistic spectrum disorder (ASD), intermittent explosive disorder (IED), or attention-deficit hyperactivity disorder (ADHD) [1].

A common feature of aggressive behavior is the reduced ability to *process emotions* and *control impulsive conduct* (behavior regulation) [2–4]. Specific areas of the brain are specialized in these two main functions. Evidence points to dysfunctions in the amygdala and prefrontal brain regions as key contributors to aggressive behavior. The amygdala, in particular, shows varied responses: reduced responsiveness to fearful faces may impair the recognition of distress cues and empathy, leading to deficient control of aggressive behavior [5]. This is aligned with the violence-inhibition mechanism model [6], suggesting a lack of empathy due to impaired distress recognition. Conversely, some studies indicate hyperresponsiveness of the amygdala in certain contexts, reflecting excitement about brutal situations [7]. This suggests that the amygdala’s role in aggression may differ based on the emotional context, such as anxiety-induced aggression versus emotional insensitivity [8].

Moreover, the prefrontal brain regions, including the orbitofrontal and ventromedial prefrontal cortices, as well as the dorsal anterior cingulate cortex (ACC), exhibit dysfunctions associated with aggressive behavior. These regions are crucial for regulating affective responses, and their dysfunction may result in reduced ability to restrain aggressive impulses. Specifically, the orbito-frontal cortex (OFC) is critical for evaluating the reward and punishment values of stimuli. It also contributes to the regulation of emotional responses, social behavior, and is involved in inhibiting inappropriate responses and controlling impulses [9]. The ventro medial prefrontal cortex (vmPFC) is integral to decision-making, emotion regulation, and social cognition [10]. Its extensive connections with various brain regions (such as the amygdala, dorso-lateral PFC, hypothalamus, ACC, etc.) facilitate these complex functions. The vmPFC is strongly connected to the ACC, which is involved in emotion regulation, error detection, and reward-based learning. Abnormalities in these areas have also been observed during reinforcement processing, indicating deficient learning mechanisms related to social rules and appropriate behavior.

Additionally, the capacity of correctly perceiving body states (interoceptive accuracy), relates to interpersonal problems, including aggression. Interoption refers to the process by which the central nervous system (CNS) receives and integrates information about the internal state of the body. The parasympathetic nervous system (PNS) and sympathetic nervous system (SNS) are also two major ascending pathways to transmit interoceptive signals to the CNS. Interoceptive signals are firstly processes in subcortical areas of the brain and then projected to higher brain regions including hypothalamus, insula, ACC and somatosensory cortex for integration [11]. Firstly, primary interoceptive information is relayed from thalamus to insula where the integration with exteroceptive signals is performed. The insula, especially, the anterior cortex is strongly connected to the OFC, ACC and PFC, which may be involved in linking interoceptive with emotional or cognitive states, and in generating regulatory signals that are sent back to lower brain regions associated with interoceptive descending efferent systems.

Difficulties in self-regulation (which includes inhibitory control) linked to interoception can contribute to these problems in individuals with borderline personality disorder (BPD) symptoms [12]. Our internal emotional state shapes our perceptions of others. During a stressful interview, the researchers found that participants with lower interoceptive accuracy were more likely to misattribute their own stress responses to negative traits in the interviewers, perceiving them as less helpful or more hostile. In contrast, individuals with higher interoceptive awareness were better able to distinguish their internal stress from external cues, leading to more accurate and unbiased social judgments. These findings highlight the role of interoception as a protective factor in reducing social misperceptions during emotionally charged situations [13].

The amygdala and PFC, along with many other brain regions, are connected to the hypothalamus [14], which regulates the sympathetic and parasympathetic branches of the autonomic nervous system (ANS) that innervate the heart, sweat glands, and other organs. As a result, the activation or deactivation of these areas induces changes in heart rate, blood pressure, skin temperature, respiration rate, and sweating, leading to a certain level of physiological arousal. Consequently, the detection of peripheral activity could help patients identify their emotions. For example, it is known that heart rate is accelerated or reduced by the activity of the SNS and PNS, and, for this reason, it can be associated with emotional dysregulation [15]. Some authors have monitored heart rate and its variability concerning aggressive episodes using off-the-shelf wearables [16]. Elevated heart rates can occur during an outburst, although authors did not find conclusive results due to the population size used (3 participants). Another study has also reported significant differences between diminished HRV in people with IED, depression, and post traumatic stress disorder (PTSD) when compared to healthy volunteers [17]. Similarly, other studies focused on skin sweating, such as that of Tonacci *et al*. [18] observed higher levels of sympathetic arousal in SCL for anger and sadness stimuli in children with aggression problems, and Deutsch *et al*. [19] detected an increase in skin conductance in subjects with outbursts of combative behavior.

Aggressive behavior is frequent during childhood and adolescence, which can significantly disrupt the functioning of both the child and their family. The onset of aggressive behavior at earlier ages is linked to higher biological risks and often results in life-course persistent antisocial behavior. A better long-term prognosis, leading to a relatively normal daily life, is more likely when aggressive behavior emerges at older ages [20]. For this reason, it is important to apply treatment at an early age. There are two types of non-exclusive treatments: drug administration and psychological therapy. The former addresses symptoms by altering the biochemistry of the patient’s brain, thereby reducing the expression of the disorder. However, no pharmacological treatment has yet targeted the core symptoms of disorders such as ASD, which include social and communication deficits, repetitive behaviors, restricted interests, and abnormal sensory processing [21].

We focus on equipping individuals with the necessary skills to manage their behavior through psychological therapy. This therapy is enhanced by using technological devices that help identify internal states through the use of physiological signals (biofeedback), like HRV, that enchance interoception, and allow warning individuals of an imminent aggressive outburst. Biofeedback is a well-known technique that has been tested in several areas, for example, to improve attention in children with ADHD through a game which an avatar that has to reach a target by modulating the beta activity obtained from frontal areas [22, 23], or in the treatment of depression [24].

It has been shown that neuronal activity can be modulated by peripheral biosignals. In [25] it was observed that respiratory rate, both spontaneous and voluntarily controlled, decreased alpha band power in phases in inspiration and increased with expiration in sensorimotor areas. The use of biofeedback based on SCL has shown an effective decrease in anxiety, with a significant reduction in sympathetic activation and sympathetic balance [26]. Likewise, the use of HRV in a biofeedback system showed that an increase in this parameter in the resting state decreased negative emotions [27], and proven useful in in regulating stress [28]. Other biofeedback methods have included the use of electromyography (EMG) to allow managing pain conditions sucessfully [29].

The main goal of this study is to verify the efficacy of psychological treatment, in the young population, when this treatment includes biofeedback of changes in some physiological features (such as SCL, HR and HRV) associated with the imminent onset of an aggressive outburst. Apart from the main goal, other aspects will also be explored: how aggressive episodes influence physiological signals (HR, HRV, SCL in particular) identifying the most significant features; and how different scenarios (home, lab) influence this variability in physiological signals.

## Materials and methods

### Participants

As explained above, the early onset of aggressive behavior is linked to higher biological risks and often leads to persistent antisocial behavior, highlighting the importance of applying treatment at early age. For this reason, the group to be studied will consist of 70 participants aged 10–16 years. They will be recruited from the INEBIR clinic, where the experimental sessions will be carried out, and other participants will be recruited from the Instituto Hispalense de Pediatría. The sample size was by analyzing the differences of the means according to a Student’s t with a confidence level of α=0.05, a test power of 1−β = 0.8 and a moderate effect size [30]. A moderate effect size (Cohen’s d = 0.5) represents a practically meaningful difference in the context of clinical decision-making, even if smaller effects may also be statistically detectable in larger samples and it is a commonly used convention in behavioral and clinical research when planning exploratory studies [31]. A moderate effect size results in 62 participants. For a small effect size (Cohen’s d = 0.2), we would need to recruit more than 300 participants, and we do not have the human and material resources to complete this study in a relatively short time. Additionally, to account for potential non-response or dropout, we included an additional 10%, bringing the final target sample size to 70 participants. This approach ensures sufficient power to detect differences between groups while anticipating common challenges in recruitment and retention.

To participate in this study, the following inclusion criteria will be applied:

Adolescents aged 10 to 16 whose parents seek professional help because their son or daughter exhibits aggressive outbursts that they are unable to manage.Intermittent aggressive episodes with a frequency of at least once a week in the two months prior to the start of the intervention.Not presenting some of the following:History of bipolar or psychotic disorder.Head trauma with loss of consciousness for more than 60 minutes.

Participants will be randomly divided into two groups: a control group (children who will not receive the experimental treatment based on biofeedback), and an intervention group, with an equal number of participants in each group. To avoid bias and to have the groups as balanced as possible, the allocation will be done in two stages. In the first, the subjects are divided by age range and biological sex, so that four subgroups are created, male between 10–13 years and between 14–16 years, and female between 10–13 years and between 14–16 years. Finally, in the second phase, individuals from each subgroup are randomly assigned to the control or intervention group, using a computer-generated sequence of random numbers and maintaining a balance between the groups, ensuring unbiased distribution. Participants’ names will be blinded by the recruiting staff from the INEBIR setting.

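### The 62 participants given for d = 0.5 match the requirement per group, not in total: power is about 49% two-sided, not the stated 80%

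*Protocol article*

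**What the plan says.** All the sizing statements are in the Participants section of the protocol article.

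- Method: "analyzing the differences of the means according to a Student’s t".
- Error rates: "with a confidence level of α=0.05" and "a test power of 1−β = 0.8 and a moderate effect size". Whether the test is one- or two-sided is not stated.
- Target effect: "A moderate effect size (Cohen’s d = 0.5) represents a practically meaningful difference".
- Result: "A moderate effect size results in 62 participants". A 10% allowance for dropout then brings the target to 70.
- Comparison case, d = 0.2: "we would need to recruit more than 300 participants", which is ruled out for lack of resources.
- Conclusion: "This approach ensures sufficient power to detect differences between groups".

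The Abstract and the Participants section both give 70 as the size of the whole trial. The randomisation paragraph divides it into a control and an intervention group, "with an equal number of participants in each group". The analysis section on assessing cognitive therapy with biofeedback compares pre-to-post differences between these two independent groups, by Mann-Whitney-Wilcoxon or one-way ANOVA. With two groups, one-way ANOVA is equivalent to the two-sided t-test.

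**The concern.** For two independent groups, alpha 0.05, 80% power and d = 0.5, the familiar answer is a little over 60 in each group. Here 62 is the total, so each arm has about half of what the stated power requires.

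The power claim is explicit, and the article's main goal is to verify efficacy. A reader of a non-significant result would assume that the trial had an 80% chance of detecting the effect the authors call meaningful. In fact the chance is close to even, so such a result would say little about whether biofeedback adds anything.

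**Working it through.** **Inputs (Participants section).** Alpha = 0.05, power = 0.80, d = 0.5 (standardised, so SD = 1), two equal groups, 62 evaluable in total (31 per arm), 70 randomised (35 per arm). Sidedness is not given, so both cases are shown.

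**1. Reproducing the plan's figure.** Normal approximation, per group:

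n = 2(z_alpha + z_beta)² / d²

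- Two-sided: 2(1.960 + 0.842)² / 0.25 = 62.8 per group with unrounded quantiles, rounded up to 63 (126 in total). The exact noncentral t gives 63.8, so 64 per group (128 in total).
- One-sided: 2(1.645 + 0.842)² / 0.25 = 49.5 per group. The exact t gives 50.2, so 51 per group (102 in total).
- One-sample or paired t-test: 34 two-sided, 27 one-sided.

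No variant gives 62 as a total. As a per-group number, 62 is the two-sided 62.8 without rounding up, and 62 per group gives 78.9% power by the exact t.

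**2. Dropout step.** 62 / 0.9 = 68.9 and 62 × 1.1 = 68.2, so 70 is about right for the 10% allowance. The error lies in the 62, not in this step.

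**3. The d = 0.2 figure.** Two-sided, 2(1.960 + 0.842)² / 0.04 = 392.4 per group; the exact t gives 393.4, so 394 per group and 788 in total. One-sided, the exact t gives 309.8, so 310 per group and 620 in total. More than 300 is true of either total, but it has the size of a per-group number.

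**4. Power delivered for d = 0.5.** Noncentrality = d × √(n/2).

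- n = 31: 0.5 × √15.5 = 1.969. The critical values on 60 df are 2.000 (two-sided) and 1.671 (one-sided).
- n = 35: 0.5 × √17.5 = 2.092. The critical values on 68 df are 1.995 and 1.668.

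| Evaluable | Per arm | Power, two-sided | Power, one-sided | d with 80% power, two-sided | d with 80% power, one-sided |
|---|---|---|---|---|---|
| 62 | 31 | 49.1% | 61.8% | 0.72 | 0.64 |
| 70 | 35 | 54.1% | 66.5% | 0.68 | 0.60 |

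**5. Mann-Whitney alternative.** Its asymptotic relative efficiency under normality is 0.955. Then 31 × 0.955 = 29.6 effective per arm, and two-sided power is about 47%.

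**6. Total that would match the stated power.** 126 to 128 evaluable, or 140 to 143 randomised after division by 0.9.

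**The case against.** **The per-group origin is an inference.** The article does not say that 62 was a per-group result, and the exact per-group answer is 63 or 64. This stands, and the explanation should be put as likely. The error does not depend on it: 62 in total does not give 80% power for d = 0.5, however the number arose.

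**The d = 0.2 figure is weak support.** More than 300 is literally true of a total near 790. As a per-group number it is closer to the one-sided 310 than to the two-sided 394, whereas 62 fits only the two-sided case. This also stands. That figure is understated rather than false, and the conclusion does not rest on it.

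**The 49% depends on assumptions.** It takes a two-sided test and a loss of 8 of 70 (11.4%). The fair range is 49% to 54% two-sided and 62% to 66% one-sided. None of these reaches 80%.

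**Pre-post data could raise power.** If d were defined on the SD of the final score, adjustment for baseline would need 1 − r² = 31/63 = 0.492, so r of about 0.71, for 62 participants to suffice. Simple change scores would need 2(1 − r) = 0.492, so r of about 0.75. The article assumes no correlation and plans no adjustment. If d refers to the change scores themselves, nothing is gained.

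**The authors may not read a null result as inefficacy.** Study limitations says the therapy period may be too short and provides for repeating S6–S9 if no change is seen. That tempers any prediction of how the authors would interpret a null result. It does not make the power statement correct, and low power makes it more likely that no change will be seen.

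**Conclusion.** The concern holds and must be fixed. With the article's own test, alpha, power and effect size, the requirement is 128 evaluable participants two-sided (102 one-sided), against the 62 stated. Power for d = 0.5 is 49% two-sided with 62 evaluable and 54% if all 70 are evaluable. Even the most favourable reading, one-sided with no dropout, gives 66%.

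These figures assume equal arms, normal outcomes with a common SD, and d defined on the scale that is compared between groups. Since the number and the power claim are both stated, a separate analysis plan could not make 62 right for these inputs.

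**What to change.** Keep 70 participants and correct the Participants section:

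1. Replace the 62-participant statement with, for example: 62 evaluable participants (31 per arm) give 80% power for d = 0.72 and 49% power for d = 0.5, at two-sided alpha 0.05. Add the figures for 35 per arm (d = 0.68 and 54%).
2. State that the test is two-sided or, if one-sided is intended, say so and use the one-sided figures.
3. Give the d = 0.2 requirement as about 790 in total (two-sided).
4. Delete the claim of sufficient power. State that the size is set by resources and that a non-significant result does not exclude d = 0.5.
5. If a baseline-adjusted analysis is adopted, give its power with the assumed pre-post correlation shown.

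The cost is wording only, with no added participants or procedures. The stated power becomes less favourable. Keeping the 80% claim for d = 0.5 under the present analysis would instead mean randomising about 140 to 143.

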**Tentative participants’ recruitment dates.**

Recruitment will start in September 2025, and it is expected to take approximately one month. Data collection and results are anticipated to be completed by March 2026 and July 2026 respectively.

### Sessions

Participants who belong to the intervention group will perform a total of eight one-hour-a-week laboratory sessions (S2–S9), while the control group will attend seven sessions (S2–S4, S6–S9). The intervention group has an additional session, S5, to help participants identify the physiological values before aggressive outburst through biofeedback. Both groups will have in common an informative and strategy selection session (S0) and one at-home session (S1) to capture some biosignals and record videos that include aggressive episodes. Figs 1 and 2 show the chronological order of the blocks and sessions in the experiment.

**Fig 1 pone.0327361.g001:**
[figure not shown]
Schedule of enrollment, interventions, and assessments in accordance with Spirit recommendation.

**Fig 2 pone.0327361.g002:**
[figure not shown]
Experimental session schedule. The experiment consists of three main blocks. 1) Initial Block, which includes two sessions: Session 0 (S0) (providing information to parents and the recruitment of participants); and Session 1 (S1) (recording at home using a smartwatch and a spy camera). 2) Second Block, which includes three sessions (S2-S4) where physiological signals are recorded before, during, and after an aggressive event. Each session consists of the following phases: baseline recording; relaxation using virtual reality (VR); evocation of the aggressive outburst by watching a prerecorded video clip; and relaxation. 3) Final Block: The subsequent sessions follow a similar phase arrangement as the second block, except for the last part. For intervention group participants, this phase will be replaced with cognitive therapy (S6-S9) with biofeedback and a session dedicated only for recognition of biofeedback signals (S5). For controls, the last phase will be replaced with cognitive therapy (S6-S9) without biofeedback.

